### Description of Interventions

#### Experimental Group

The participants in the experimental group will receive the VirTele program. VirTele is an 8-week home program during which participants will use the Jintronix exergame [10] for UE training and the Reacts telerehabilitation application [20] to conduct videoconferenced sessions with the therapists (physical therapists or occupational therapists). All the equipment necessary for the proper functioning of the VirTele program, including the computer, the Kinect camera, the Reacts, and Jintronix software as well as a constant internet accessibility (USB internet key), will be provided for free to the participants. A technician will oversee the transport and the installation.

#### Telerehabilitation Component

The Reacts application is an interactive audio-video platform that allows secure communication between therapists and participants using standard computer or tablet technologies [20]. The application enables a live game access when it is used in combination with Jintronix. Thus, the therapist will be able to see the participant doing exercises and see the exergame platform while it is being used. The access to the live game platform allows the therapist to track the tasks or movements required by the game and see how the participant manages to accomplish them to adjust the difficulty level of the game according to the participant’s motor skills and interest. The Web sessions with Reacts will take place three times a week for 2 weeks, twice a week for 2 weeks, and then once a week for the remaining 4 weeks.

Reacts can also be used alone, making it possible for the participant to interact with the therapist when finishing the exercises. These sessions provide an opportunity to discuss difficulties regarding playing games and to subsequently modify the rehabilitation program according to the participant’s abilities and preferences. This shared decision-making process can help foster motivation to make health-related decisions (eg, setting goals weekly with the therapist, determine the optimal level of difficulty of the exercises, and choosing the games) and specially to continue rehabilitation after the end of the intervention. This shared decision-making process will aim to increase the empowerment of the participant, facilitating subsequently the transfer of the functional gains acquired in the context of the study into real life. This transfer occurs by identifying ways of reproducing the tasks of the game in activities of the daily life and increasing the use of the affected UE in the long term. Participant empowerment will be further encouraged by using motivational interviewing based on self-determination theory (SDT) principles during telerehabilitation sessions [21,22]. This theory states that humans naturally tend to achieve changes that respect and enable the satisfaction of their three basic psychological needs, namely, (1) autonomy, (2) connectivity, and (3) competence [22,23]. There are two regulation processes predicting behavioral engagement and maintenance: the behavior emanating from intrinsic motivation and the internalization of extrinsic motivation [23].

#### Virtual Reality Component

The Jintronix exergame consists of six UE games played for varying amounts of time and at different difficulty levels (speed, precision, and range of movements), which can be tracked remotely by the therapist asynchronously through the data provided in Jintronix Web-based portal. The therapist is also able to modify the difficulty parameters according to the performance data recorded on the portal. This exergame uses a Kinect camera, which captures the person’s body movements without wearing sensors. Participants will be invited to use Jintronix at least five times a week for 8 weeks, for 30-min sessions, performing a total of 20 hours of exercise. A minimum of 15 hours is suggested for an intervention to result in a moderate improvement in activities related to daily living following a stroke [6].

Jintronix includes an automated log system, which records the active time spent by participants in each game and the score achieved. The therapist can access the exergame interface at any time to monitor the participant’s progress and adherence to the exercise program and modify the difficulty level.

Before starting the intervention, therapists will receive training in motivational interviewing [24] to ensure a client-centered rehabilitation program that aligns with the SDT [21]. We used SDT [23] as a conceptual framework to guide the VirTele intervention to empower the participant and solicit their interest and motivation for the treatment plan that the therapist and participant will decide on together. The combination of the telerehabilitation system (Reacts) and the Jintronix exergaming system aims to foster participant-therapist interaction throughout the rehabilitation program and to develop a partnership relationship based on information sharing and trust. It is in this perspective that SDT was integrated. Its constructs were used as a basis for a discussion plan which the therapist refers to during videoconferenced sessions.

All participants in the experimental group will participate in a 30-min training session with the technician responsible for the installation of the technology to learn to use the VirTele technology.

#### Control Group

The participants in the control group will receive GRASP based on their UE function. It includes strengthening exercises of arm and hand, range of motion, and functional arm activities [5]. The program includes some equipment such as a ball, a bean bag, or paper clips. The participants will be invited to carry out the GRASP exercises over the 8 weeks, 5 days a week for 30 min each day, performing 20 hours of exercises in total (same as experimental group). A paper log journal will be provided to track the amount of time spent on the exercises and the number of sessions as well as any adverse events (fatigue and pain). The control group will not receive any follow-up with the therapist, but at the end of the study, the participants will be offered one session with the therapist to discuss strategies for improving long-term UE function. Before starting the intervention with GRASP, the participants will receive a 30-min training session for using the program equipment by one of the therapists included in the study.

### Data Collection

#### Quantitative Data

At study entry, the participant’s sociodemographic information (gender, age, civil status, language, number of years of education completed, primary occupation, and stroke characteristics) will be collected for descriptive purposes.

For the randomized, blinded feasibility trial, several outcomes measures will be used to address the different objectives. The first objective of the trial is to determine the preliminary efficacy of VirTele on UE motor recovery, function, quality of life, and motivation, in participants with chronic stroke, compared with conventional therapy (GRASP).

The Fugl-Meyer Upper Extremity Assessment will be the primary outcome to determine the efficacy of the technology for UE motor control recovery. This is a performance-based measure of UE impairment [25,26]. It includes 13 items scored on a 3-point ordinal scale of 0 to 2 [26]. The Fugl-Meyer Upper Extremity Assessment has been shown to have good internal consistency (alpha=.82-.84) and good concurrent validity (r=0.74) [25].

The secondary outcomes are self-reported questionnaires and include the Motor Activity log 28 [27,28], the Stroke Impact Scale-16 [29,30], and the Treatment Self-Regulation Questionnaire-13 [31].

The Motor Activity log 28 is a self-reported measure of UE use [27,28]. This rates the quality and frequency of use of the UE in 28 everyday tasks and is administered by interview [27,28]. The Motor Activity log 28 demonstrated high reliability (r=0.82) and high validity, with excellent concurrent correlation with Stroke Impact Scale hand function scores (r=0.72) [32]. The impact on quality of life will be determined using the Stroke Impact Scale-16, a stroke-specific, self-reported, health status measure consisting of 16 items concerning daily activities [29,30]. The Stroke Impact Scale-16 has been shown to have good internal consistency (alpha=.87) and a good convergent and discriminant validity [33]. Motivation will be measured using the Treatment Self-Regulation Questionnaire-13 [31], a 13-item questionnaire that has been developed to measure treatment motivation, aligned with SDT. The Treatment Self-Regulation Questionnaire has been shown to be reliable with a high internal consistency (alpha=.73-.95) and valid across health care contexts and has been used in rehabilitation [34]. The two regulation processes of the SDT (intrinsic and extrinsic motivation) are targeted in the form of subscales in the Treatment Self-Regulation Questionnaire-13 [31]. The use of this questionnaire allows us to investigate the impact that the motivation could have on adherence to the program and its effectiveness.

The second objective of the randomized, blinded feasibility trial is to assess the feasibility of using VirTele with participants diagnosed with stroke at home. Feasibility data include indicators of process, resources, management, and scientific feasibility [35]. In Table 1, we describe all the outcomes that will be used for each indicator. These data will also provide evidence to examine the validity of the research protocol to inform the planning of a larger clinical trial.

A trained assessor who is not involved in the delivery of interventions and blinded to group assignment will be responsible for the face-to-face administration of the outcome measures.

**Table 1 table1:** Description of feasibility indicators outcomes.

Feasibility indicators		Outcomes
**Process**		
	Recruitment rate	Percentage of participants who meet the eligibility criteria and accept to participate (20%) Rate of participants per month Duration of recruitment
	Retention rate	Percentage of participants who complete the 2-month intervention with telerehabilitation with virtual reality
**Resources**		
	Exercise adherence rate	Percentage of participants who complete 150 min of Jintronix exercises per week
	Number and duration of sessions	These data will be obtained from the Jintronix exergame and Reacts app system
	Frequency and time spent by the therapist assisting for real-time sessions with Jintronix	Logs completed by the therapist at the end of each session
	Resources utilization	Logs completed and time spent by therapists and technical staff
**Management**		
	Technical problems with the technology	Obtained from a log maintained by the study therapists and technical team
	The role of the shared decision making and empowerment in achieving task goals	Encourage participants to report new task goals every week Percentage of participants who achieved the goals set with the therapist Percentage of task goals achieved per participant
**Scientific**		
	Safety	Occurrence of adverse events (pain, falls, motion sickness, dizziness, exertion, fatigue, and headaches) will be documented by a computerized participant log
	Satisfaction	With the technology: the Modified Short Feedback Questionnaire [36] With the interaction between the therapist and the participant: Health Care Climate Questionnaire (Perceived Autonomy Support) [37]
	Size of sample	The calculation will be done from the size of the treatment effect or the variance of the treatment effect

#### Qualitative Data

Individual semistructured interviews of 30 min will be conducted with the first 10 participants from the experimental group (n=10) after the end of 8-week intervention. The interview guide will be developed based on the Unified Theory of Acceptance and Use of Technology (UTAUT) conceptual framework [38]. This theory includes four essential constructs (expected performance, expected effort, social influence, and facilitating conditions), which are considered as direct determinants of the intention and behavior of adoption and the use of new technologies by stakeholders [38]. Therefore, semistructured interviews will be used to inform not only the intention and behavior of adoption and use of VirTele by participants diagnosed with stroke and therapists but also of UE use in the future (through UTAUT constructs). When combined with SDT constructs, the interview will inform the participants’ empowerment and the shared decision-making process underlying the therapist choice of games and difficulty levels.

The study therapists will also be interviewed to describe their experience with VirTele (obstacles and facilitators), explore their behavior to see if they align with SDT, and investigate the shared decision-making process underlying their choice of games and difficulty levels. Individual semistructured interviews of 30 min will be used. The UTAUT and the SDT will serve as basis for the interview guide development.

All interviews will be voice recorded and transcribed verbatim. A logbook and reflective notes will also be taken.

### Data Analysis

#### Quantitative Data Analyses

Statistical analysis of the quantitative data will be performed using the Statistica software. Descriptive statistics will be used to report sociodemographic characteristics of participants (age, gender, handedness, and stroke characteristics) in both groups (experimental vs control). To address the first objective of the randomized, blinded feasibility trial, a mixed model approach will be applied for primary and secondary outcomes measure. Each model will contain one between-subject effect factor (group: control vs experimental), one within-subject effect factor (time: T1, T2, T3, and T4), and two covariates (gender and age) factors, which may impact exergame use. For each outcome measures, residual plots will be examined to verify normality and identify the best covariance structure. All the outcomes measure changes will be compared with the minimal clinically important differences. The effect size of the comparison between experimental and control groups will be calculated to estimate the final sample size. To address the second objective of the randomized, blinded feasibility trial, descriptive statistics (frequencies, means, and standard deviations) will be used to highlight the amount of exercise performed, the occurrence of adverse events, and participant and therapist satisfaction level in the experimental and control groups.

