### Study Objectives

Given the evidence for the efficacy of exergames as well as telerehabilitation for stroke rehabilitation, but the limited evidence of combining these technologies, such as in the VirTele program, the overall goals of this study are to explore its preliminary efficacy for UE rehabilitation and examine its feasibility for use with stroke survivors at home. More specifically, the objectives of this study are to (1) determine the preliminary efficacy of VirTele on UE motor recovery, function, quality of life, and motivation in participants with chronic stroke, compared with conventional therapy (GRASP); (2) examine the feasibility of using VirTele with participants diagnosed with chronic stroke at home; and (3) identify the obstacles and facilitators for the technology use by participants diagnosed with stroke and stroke therapists and understand the shared decision-making process.

It is hypothesized that the exergame-telerehabilitation program will lead to greater UE motor recovery than usual care (GRASP) in participants with chronic stroke. We also hypothesize that the exergame-telerehabilitation program will have a greater impact on function, quality of life, and motivation in participants with chronic stroke.

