## Methods

### Study Design

This is a mixed method study design consisting of a randomized, blinded feasibility trial with an embedded multiple case study that will take place in Montreal, Canada. The randomized feasibility trial is a two-arm, single-blind trial design in which eligible participants will be randomly allocated to an experimental (VirTele for 8 weeks) or control, usual care group (GRASP for 8 weeks). The feasibility trial captures both feasibility and preliminary efficacy outcomes. Publishing the feasibility results would provide a better understanding of the context in which the efficacy data were collected and a better interpretation of the final results [13,14].

Outcome measures will be assessed for both groups on four occasions: at baseline (T1), at the end of 2-month intervention (T2), after a 1-month follow-up period (T3), and after a 2-month follow-up period (T4; Figure 1).

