### Data Collection

Participants will be recruited from different sites to increase the representativeness of the target population in the region. The control group will not receive any motivational interviewing or follow-up to keep the standard aspect of therapy that corresponds most to the clinical reality. This will enable us to identify the added value of the VirTele program compared with GRASP. After outcome measures collection in T1 and T2, to compare the effect of each intervention within and between groups, we will collect additional measures at T3 and T4 to evaluate the retention of gains.

The multiple case study provides an in-depth description of stakeholders use experience and potential use of VirTele program. In this study, we will have two case groups: participants diagnosed with stroke and study therapists (physical therapists or occupational therapist). Each of these cases experiences the intervention differently, and it is therefore essential to report them through interviews. The variation of the cases makes it possible to increase the variation of the experiences and thus to increase the robustness of the qualitative results [19]. UTAUT and SDT will serve as a basis for establishing certain links between the concepts that will emerge (Multimedia Appendix 1).

The results of this study will allow to verify if all elements of the protocol work well together to conduct a broader future study. We have tried to provide as much detail as possible about the various processes and steps of the protocol to facilitate its reproduction by other studies that seek to develop tools for the remote management of chronic diseases.

This project will also provide preliminary evidence of the efficacy of VirTele on motor and functional recovery of the UE following chronic stroke for future guidelines review, although studies caution us about solely using results from feasibility studies to establish intervention efficacy [35].

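### The efficacy model is listed without a group-by-time term, a baseline adjustment or a named T2 contrast, so as written no term tests greater recovery with VirTele

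*Protocol article*

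**What the plan says.** All places are in the protocol article.

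- **Model (Quantitative Data Analyses).** A mixed model is planned for the primary and secondary outcomes: "Each model will contain one between-subject effect factor (group: control vs experimental), one within-subject effect factor (time: T1, T2, T3, and T4", with "two covariates (gender and age) factors, which may impact exergame use". The list stops there.
- **Covariance (same section).** "residual plots will be examined to verify normality and identify the best covariance structure".
- **Use of the comparison (same section).** "The effect size of the comparison between experimental and control groups will be calculated to estimate the final sample size".
- **Visits (Study Design).** Outcomes are measured "at baseline (T1), at the end of 2-month intervention (T2", and again one month (T3) and two months (T4) into follow-up. T1 therefore precedes treatment.
- **Hypothesis (Study Objectives).** The "exergame-telerehabilitation program will lead to greater UE motor recovery than usual care (GRASP", that is, a between-arm difference in change.
- **Purpose of the visits (Discussion, Data Collection).** The first two visits serve the effect comparison: "After outcome measures collection in T1 and T2, to compare the effect of each intervention within and between groups". The two later visits have a separate role, described in the same sentence: "we will collect additional measures at T3 and T4 to evaluate the retention of gains".

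The last passage gives T2 and T3/T4 different roles, but the article links those roles to no model term or contrast.

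**The concern.** A hypothesis of greater recovery concerns how the arms diverge after T1. In a model with only the listed terms, the time effect is shared by both arms and cannot show divergence. The group effect is one between-arm difference averaged over four visits. Randomisation makes the expected difference zero at the first of these, so T1 pulls the estimate towards zero. Any chance imbalance at T1 also enters the estimate.

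Two things are at stake. The first is whether the analysis answers objective 1. The second is the effect size for the later trial, since supplying it is a stated purpose of this study. If it came from the four-visit group term it would be too small.

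A related gap remains even if the interaction was intended. A group-by-time test over four visits has (2-1)×(4-1) = 3 degrees of freedom and does not say which between-arm difference is the primary result.

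**Working it through.** **Inputs.** From the article: four visits with T1 before treatment, 26 per arm, 20% loss. Retained per arm: 26 × 0.8 = 20.8, taken as 21. Assumed, because the article gives no values: between-arm effect d in SD units, constant over T2-T4; equal correlation r between any two visits; SD 1 at each visit; complete data on those retained; two-sided alpha 0.05. Age and gender are ignored in the power figures. The article states no power or effect figure for a particular model term, so there is no plan figure to reproduce on this point.

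**1. What the literal group term estimates.** Under equal correlation each visit has weight 1/4.
- Constant effect: (0 + d + d + d)/4 = 0.75d.
- Effect fading to half by T4: (0 + 1 + 0.75 + 0.5)/4 = 0.5625, or 56% of the T2 effect.
- A simulation of the additive model (60 data sets, 26 per arm, r = 0.7, d = 0.5) gave a mean group coefficient of 0.40 (simulation SE 0.03), consistent with 0.75 × 0.5 = 0.375.

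**2. Baseline imbalance.** A chance T1 difference b enters the group term with weight 1/4 directly, and also through the correlated later visits. Its expected shift is b(1 + 3r)/4, which at r = 0.7 is 0.775b.

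**3. Standard errors and power at d = 0.6, r = 0.7, 21 per arm.** Noncentral t with 40 df; noncentral F for the interaction.
- Literal group term: SE = √[(2/21)(1 + 3×0.7)/4] = 0.272; target 0.75 × 0.6 = 0.45; power 37%.
- Unadjusted T2-T1 contrast: SE = √[(2/21) × 2(1 - 0.7)] = 0.239; target 0.6; power 69%.
- 3-df interaction: λ = 0.75 × 0.6² × 21/[2(1 - 0.7)] = 9.45; F on 3 and 120 df; power 72%.
- Baseline-adjusted T2 contrast: SE = √[(2/21)(1 - 0.7²)] = 0.220; target 0.6; power 76%.

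**4. Sensitivity (same formulas).**

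| d | r | Literal group term | T2-T1 | 3-df interaction | Adjusted T2 |
|---|---|---|---|---|---|
| 0.4 | 0.7 | 19% | 37% | 36% | 43% |
| 0.6 | 0.5 | 44% | 47.5% | 48% | 59% |
| 0.6 | 0.7 | 37% | 69% | 72% | 76% |
| 0.6 | 0.8 | 34% | 85% | 89% | 89% |
| 0.6 | 0.9 | 32% | 99% | >99% | 99% |

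The literal group term is lowest in every row. The advantage of the adjusted T2 contrast over the 3-df test is 11 points at r = 0.5 and 4 points at r = 0.7 (d = 0.6), and has gone by r = 0.8.

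**5. Effect size carried forward.** If the later trial were sized on 0.75d with the same SD, its sample size would be multiplied by 1/0.75² = 1.78.

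**The case against.** The strongest reply is that the article lists factors, not terms. Naming one between-subject and one within-subject factor is common shorthand for a design whose test is their interaction. The text never says that only main effects will be fitted, nor that the group main effect is the test. The hypothesis of greater recovery and the stated purpose of T1 and T2 both fit an interaction. The sample size leans the same way, though weakly, because the Sampling section gives no test family, effect metric or correlation. Reading 0.2 as Cohen's f, an interaction with three measurements and r = 0.5 needs 42, or 42/0.8 = 52.5, rounded up to 53, with loss. A four-visit group main effect needs 96 to 156 before loss (r from 0.3 to 0.7).

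This reply stands as far as it goes. Several stronger readings are therefore not supported:

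- **That the trial will report a diluted effect, or that its power is about half what it could be.** Both follow only if no interaction is fitted and the group term is the test. Otherwise dilution disappears, and the comparison at 0.6 SD and r = 0.7 is 72% or 69% with 76%.
- **That the later trial will be wrongly sized.** The article says the effect size comes from comparing the groups. It does not say from which coefficient, and Table 1 is no more specific.
- **That the covariance sentence implies a known type I error.** The plan names no structure, so no error rate can be attached to it.
- **That age and gender are wrong covariates.** They are acceptable and can stay.

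It may also be said that such detail belongs in an analysis plan. That holds for degrees-of-freedom methods and convergence fallbacks. It does not hold for the model's contents, which the article states. Nor does the feasibility label remove the point, because preliminary efficacy is objective 1 and carries a directional hypothesis.

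**Conclusion.** The point holds as a badly fixed model statement. As written, no listed term tests the hypothesis, and the group term targets 75% of a constant T2-T4 effect while absorbing baseline imbalance. If the interaction was meant, what remains is smaller: no primary contrast is named, and baseline adjustment adds a modest amount of power at moderate correlation and almost none over the 3-df test at 0.8 or above. The article does not settle which reading is right, and that ambiguity should be removed.

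The 75% assumes equal correlations and complete data. All power figures rest on an assumed effect, correlation and number retained. The covariance sentence is secondary: residual plots can check normality, but they are not a rule for choosing a covariance structure, and the choice would be made after seeing the data.

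**What to change.** Amend the Quantitative Data Analyses section as follows.

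1. Model T1-T4 with a common T1 mean for both arms and treatment-by-visit terms at T2, T3 and T4. Alternatively, model T2-T4 adjusted for T1 score, with that adjustment allowed to differ by visit, and with treatment-by-visit terms. Keep age and gender.
2. Name the Fugl-Meyer between-arm difference at T2, with its 95% CI, as the single primary contrast and as the source of the effect size carried forward. Report T3 and T4 as retention.
3. Specify an unstructured covariance in advance (4 × 5/2 = 10 parameters if T1-T4 are all outcomes), and use residual plots for distributional checks only.

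The cost is a few sentences and a standard model. Baseline is already collected and no participants are added. The Results section says data analysis had not begun at submission; if that is still so, the change can be made in advance.

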### Sampling

To date, no studies have reported on the use of combining such technologies, such as in the VirTele program so that this randomized, blinded feasibility trial will provide evidence for the effect size. However, as the first estimate of effect size, a sample size of 52 participants has been calculated using the Fugl-Meyer Upper Extremity Assessment as a primary outcome and G*Power 3.1 [16]. We assumed a medium effect size of 0.2, which was reported in a study with chronic stroke survivors with a 2-arm randomized clinical trial [17] and accounting for 20% retention issues (alpha=.05 and power=80%). This sample size corresponds to recommendations for pilot efficacy and feasibility trials [18] and is realistic, given time and budgetary constraints as well as recruitment potential. Thus, for the randomized, blinded feasibility trial, 52 participants will be recruited and randomly allocated to the experimental (n=26) or control group (n=26). A block randomization with a block size of six will be used, given time and material constraints.

For the multiple case study component, four therapists and the first 10 participants from the experimental group will be invited to participate in interviews. However, the final sample size of the participants diagnosed with stroke will be adjusted depending on the qualitative data saturation [19].

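### Residual plots are not an adequate or reproducible rule for choosing the covariance structure of the four-visit mixed model; a wrong choice can distort standard errors and p-values in either direction

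*Protocol article*

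**What the plan says.** Under Quantitative Data Analyses, the protocol article states that "a mixed model approach will be applied for primary and secondary outcomes measure". Each model has group as the between-subject factor, time at four levels as the within-subject factor, and gender and age as covariates. The next sentence sets the selection rule, to be applied outcome by outcome: "residual plots will be examined to verify normality and identify the best covariance structure". It names no candidate structures, default or numerical criterion.

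The Study Design section places the assessments at baseline (T1) and then "at the end of 2-month intervention (T2), after a 1-month follow-up period (T3), and after a 2-month follow-up period", that is, at months 0, 2, 3 and 4. The Discussion (Data Collection) explains that T1 and T2 serve to compare the interventions within and between groups, and adds "we will collect additional measures at T3 and T4 to evaluate the retention of gains". The Sampling section plans 26 participants per arm and allows for 20% loss.

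**The concern.** In a repeated-measures model, the assumed covariance structure determines the standard error of the group difference in change from baseline. The plots normally used to check normality show the shape and spread of residuals. They do not show directly how pairs of visits correlate. Other residual displays do carry that information, but looking at them is not a decision rule: two analysts could follow the sentence faithfully, choose different structures and report different p-values. Because the choice is repeated for each outcome, the Fugl-Meyer and each questionnaire could end up with different structures, all chosen after the data are seen.

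The stakes are the intervals and p-values at T2 (end of intervention) and at T3 and T4 (retention of gains). The Study Objectives section hypothesises greater recovery with the exergame-telerehabilitation program than with the control, so between-group inference is intended.

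**Working it through.** The plan gives no figure for this point to reproduce, and no standard deviations or correlations. All correlations below are therefore assumptions. The document supplies the visit times (months 0, 2, 3 and 4) and the sample size: 26 per arm, or about 21 after 20% loss (52 × 0.8 = 41.6, taken as 42).

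**Formula.** With equal variance at each visit, taken as 1, the true variance of a person's change from T1 to Tk is 2(1 − ρ₁ₖ). With complete data, a compound-symmetry fit replaces ρ₁ₖ by the mean ρ̄ of the six pairwise correlations. The ratio of reported to true SE is then √[(1 − ρ̄)/(1 − ρ₁ₖ)], and the actual error of a nominal two-sided 5% test is approximately P(|Z| > 1.96 × ratio).

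**Compound symmetry fitted to pure serial decay, 0.90 per month.**
- Correlations: T1–T2 0.81, T1–T3 0.729, T1–T4 0.656, T2–T3 0.90, T2–T4 0.81, T3–T4 0.90. Their mean is 0.801.
- T4: fitted variance 2(1 − 0.801) = 0.398, true variance 2(1 − 0.656) = 0.688. The ratio is √(0.398/0.688) = 0.76 and the error about 13.6%.
- T3: true variance 2(1 − 0.729) = 0.542, ratio 0.86, error about 9.3%.
- T2: true variance 2(1 − 0.81) = 0.380, ratio 1.02, error about 4.5%.

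Simulation at 21 per arm (20,000 trials, decay 0.90 to 0.95 per month) gives 13.5–14.2% at T4 and 9.1–9.7% at T3.

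**The same wrong fit under other variance splits.** T4 error, simulated at 21 per arm with decay 0.90 to 0.95 per month:
- 10% measurement error, the rest decaying: about 10–11%.
- 20% measurement error, the rest decaying: about 8–9%.
- 70–80% stable between-person variance, remainder split equally between decay and measurement error: about 6%.
- 80% stable, 5% decaying, 15% measurement error: about 5.4%. As a hand check at 0.90 per month, ρ̄ = 0.8 + 0.05 × 0.801 = 0.840 and ρ₁₄ = 0.8 + 0.05 × 0.656 = 0.833. The ratio is √(0.160/0.167) = 0.98 and the error about 5.5%.

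**Errors in the other direction.** Suppose the truth is compound symmetry at 0.8 and AR(1) indexed by visit number is fitted. The fitted T1–T4 correlation is then about 0.8³ = 0.512. The SE ratio is √[(1 − 0.512)/(1 − 0.8)] = √2.44 = 1.56, and the error about 0.2%. At T3 the ratio is √[(1 − 0.64)/0.2] = 1.34 and the error about 0.85%. Simulation at 26 per arm (4,000 trials) gives 0.2% and 0.8%.

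**T2 is not exempt.** Suppose post-baseline visits correlate 0.95 with each other and 0.75 with baseline, so ρ̄ = (3 × 0.75 + 3 × 0.95)/6 = 0.85. Compound symmetry then gives a ratio of √(0.15/0.25) = 0.77 and about 13% error at T2, T3 and T4 alike. AR(1) gives 17.2% at T2 in simulation. Conversely, when the truth is AR(1) by visit at 0.8 to 0.9, compound symmetry gives only about 1.5–2.0% at T2.

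**With a better rule.** Over five assumed truths at 26 per arm, a prespecified unstructured covariance held 4.5–5.4% for the change from T1 to each later visit. AIC selection among compound symmetry, AR(1) and unstructured held 4.0–5.7%.

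**The case against.** The strongest reply has four parts.

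First, the article does not say which residual plots are meant. Residual spread by visit, visit-against-visit scatterplots and a variogram all bear on covariance. This stands: a reader might infer that residual plots cannot identify the structure at all, and the documents do not support that. What remains is that inspection is not a reproducible rule.

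Second, the article never chooses compound symmetry or AR(1). The 14% figure is therefore not the error rate of the stated rule; it belongs to one wrong choice under pure serial decay. This also stands, which is why a range is given. Nor does a wrong choice always lead to false positives; some wrong choices are strongly conservative. The unequal visit spacing argues only against AR(1) indexed by visit number. It is no evidence against compound symmetry, which assumes equal correlation at every lag.

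Third, the consequences are limited. Point estimates barely change with complete balanced data, and the Discussion itself warns against relying on feasibility results alone to establish efficacy. A reader might also infer that the next trial would be undersized. The documents do not support going that far: Table 1 bases that calculation on the size of the treatment effect or its variance, without saying which variance or visit.

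Fourth, candidate structures and degrees-of-freedom methods are commonly left to an analysis plan. That is fair for those details, and their absence is not the point. The article does state the selection method, and a plan that followed it would inherit the weakness.

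**Conclusion.** The point holds in a limited form. Choosing the covariance structure from residual plots, outcome by outcome, is a poor stated rule because it is subjective, depends on the data and cannot be reproduced. If it leads to a wrong simple structure, the damage falls on standard errors, intervals and p-values, and it can go either way at any post-baseline visit. At T4 the actual error of a nominal 5% test ranged from about 0.2% to about 14% in the scenarios examined; at T2 it ranged from about 1% to 17%. These figures assume complete data, no treatment effect and correlations that the documents do not give. They are also conditional on a wrong choice, since a correct or unstructured one stays near 5%. In a feasibility trial that calls its efficacy evidence preliminary, this should be corrected but does not undermine the design.

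**What to change.** Replace the clause with wording such as: *For every outcome, an unstructured covariance over T1 to T4 will be fitted by REML with a small-sample degrees-of-freedom correction (Kenward-Roger or Satterthwaite). If the model does not converge, heterogeneous Toeplitz and then a spatial-power structure on actual months will be used, in that order. Residual plots will be used only to check normality and variance.* An acceptable alternative is AIC over a prespecified list of structures that includes unstructured.

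The Results section says that data analysis had not begun at submission, so at that stage the rule could be fixed without reference to the results.

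Cost: the text change is short. An unstructured covariance has 4 × 5/2 = 10 parameters, estimated from about 42 to 52 participants, so some intervals may be slightly wider. The article names Statistica. Whether it offers these options was not checked, and other software may be needed if it does not.
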